**Fig. 1 Fig1:**
[figure not shown]
Study procedure

Three and six months after discharge from hospital, all patients will be contacted for a follow-up assessment. For this purpose, patients will be invited to a check-up in an outpatient clinic, where the following assessments will be repeated: Barthel Index [35], MoCA [42], TuG [44] and Tinetti [45], GDS [46], and *hand grip strength*. Additionally, the patients will be asked to answer the following questions: changes in health since the last assessment (same, better, worse, new diagnoses, changes in medication), *healthcare utilization* since the last assessment, changes in *mobility*, changes in concentration, VAS on geriatric syndromes, changes in the syndromes since last assessment (same, better, worse), and *independence* (iADLs and ADLs). Patients will also be asked to re-complete the WHOQOL-Bref [54] and the ASAS-R [49, 50]. Additionally, mortality and reason for death will be noted if necessary.

Those patients unable to come to the outpatient hospital for follow-up screening will be contacted via telephone to complete the additional questionnaires as well as the Barthel Index [35], a measure of *cognition* (immediate and delayed recall and fluency as performed in the MoCA [42]) and the GDS.

The aforementioned data collection will produce both cross-sectional and longitudinal data, enabling a comprehensive understanding of the variables at different time intervals. Separate endpoints are defined for each type of data. For cross-sectional data, the primary endpoint is *self-management*, measured using the ASAS-R [49, 50]. This will help identify factors related to self-management behaviour among older adults, including health-related, psychosocial, and environmental factors.

For longitudinal data, the primary endpoint is *independence* in daily activities. For this purpose, an additive composite endpoint is defined consisting of changes in both iADLs and ADLs. Both ADLs and iADLs are closely related and are expected to change in the same direction, allowing for a combined interpretation [59–61]. These unweighted multi-attribute endpoints assign equal importance to the included instruments and lead to an overall sum score based on all included items [59]. For this purpose, a 1-point change in *independence* is defined as a change of at least 1 point in the Blaylock Score or 5 points in the Barthel Index.

Secondary endpoints for the longitudinal data collection consist of mortality, re-hospitalization, and *QoL*, depending on *self-management*.

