### Variables and data collection

Data will be collected from patients at baseline during their hospital stay, and at two follow-up time points (3 and 6 months post-discharge, see Fig. 1 for an overview of the study procedure). Patients’ medical records as well as routine clinical assessments and additional questionnaires will be used to collect information on self-management and its related factors as well as geriatric syndromes.

During baseline data collection, each patient will undergo an encompassing geriatric assessment performed by medical staff on the wards. This includes the following assessments:

Geriatric Screening for *functioning* as proposed by Lachs [39].Level of *independence* in ADLs and instrumental ADLs (iADLs) as assessed by the Barthel Index [35] and Blaylock Score [40]. The Blaylock Score assesses independent management of finances, medication, use of transportation, grocery shopping, and meal preparation.Level of *Loneliness* as assessed by the UCLA 3-Item Loneliness Scale [41].*Cognition* (normal, mild or moderate/severe cognitive problems) as assessed by the Montreal Cognitive Assessment (MoCA) [42] or Mini Mental Status Examination (MMSE) [43].*Mobility* as measured by the Timed Up and Go (TuG) [44] and Tinetti-Test [45].*Depressive symptoms* according to the Geriatric Depression Scale (GDS) [46].*Hand grip strength* in kg as a marker for physical strength.

In addition, the following sociodemographic and health-related parameters will be taken from the patients’ medical records:

*Age, sex, highest education level, marital state* and living situation/*housing*.Use of *aids*, *care* level, *help at home*, *healthcare utilization* (e.g. number of doctor or physician consultations or regular therapy).*Diagnoses* and number of *medications*.

These assessments and parameters will serve as independent variables related to self-management. For the assessment of self-management itself and further related factors, the following self-report questionnaires were selected based on the previous literature cited above. The questionnaires will be filled out with the assistance of trained study staff:

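### Follow-up is not aligned with the baseline instruments: cognition changes test between visits, and the Blaylock Score behind the longitudinal primary endpoint is not named at follow-up

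*Protocol article*

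**What the plan says.** All of this is in the Protocol article, Variables and data collection, unless stated otherwise.

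- **Baseline independence** is measured "in ADLs and instrumental ADLs (iADLs) as assessed by the Barthel Index [35] and Blaylock Score [40". The iADL content is spelled out: "The Blaylock Score assesses independent management of finances, medication, use of transportation, grocery shopping, and meal preparation".
- **Baseline cognition** is recorded in three categories (normal, mild, moderate/severe) "as assessed by the Montreal Cognitive Assessment (MoCA) [42] or Mini Mental Status Examination (MMSE) [43".
- **Clinic follow-up at 3 and 6 months** is the visit "where the following assessments will be repeated: Barthel Index [35], MoCA [42], TuG [44] and Tinetti [45], GDS [46", plus grip strength. A further set of questions to the patient ends with "changes in the syndromes since last assessment (same, better, worse), and *independence* (iADLs and ADLs". The WHOQOL-Bref and ASAS-R are also named for re-completion.
- **Telephone follow-up** is for patients who cannot attend. They "will be contacted via telephone to complete the additional questionnaires as well as the Barthel Index [35", with the immediate recall, delayed recall and fluency tasks of the MoCA, and the GDS.
- **The longitudinal primary endpoint** is an additive composite of iADL and ADL change with equal importance for each instrument. A 1-point change "is defined as a change of at least 1 point in the Blaylock Score or 5 points in the Barthel Index".
- **Change in cognition** is among the follow-up aims in the Abstract (Methods). It is not among the primary or secondary endpoints.

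**The concern.** A change score needs the same measure at both ends. For cognition the protocol allows two tests at baseline, one of them in clinic at follow-up, and a fragment of that one by telephone. It gives no rule linking them. Whether a patient has a usable change value then depends on which test was given on the ward and on whether the patient could travel. Telephone follow-up is reserved for those unable to come, so the loss is unlikely to be random with respect to health.

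For independence, the endpoint is written in points of two named scales. One of them, the Barthel Index, is named in both follow-up routes. The other, the Blaylock Score, is named in neither. A site working from this text could record a general answer about iADLs, from which no Blaylock change can be computed. That would weaken the iADL half of the longitudinal primary endpoint, on which the aim linking self-management to later independence depends (Statistical analyses).

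**Working it through.** The protocol states no figure to reproduce here. The check sets the lists side by side and then sizes the cognition part under assumed shares.

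**Step 1. Instruments by visit**

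| Measure | Baseline | Clinic follow-up | Telephone follow-up |
|---|---|---|---|
| ADL | Barthel | Barthel | Barthel |
| iADL | Blaylock | question on independence, no instrument named | only through the additional questionnaires, no instrument named |
| Cognition | MoCA or MMSE | MoCA | MoCA recall and fluency only |
| Depressive symptoms | GDS | GDS | GDS |

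The Barthel Index and GDS line up by every route. Cognition does not, and for iADL the text does not say.

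**Step 2. What cognitive change each patient can have**

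| Baseline test | Clinic follow-up | Telephone follow-up |
|---|---|---|
| MoCA | full MoCA change | change on recall and fluency items only |
| MMSE | no same-instrument change | no same-instrument change and no total score |

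Only one of the four cells gives a full change score.

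**Step 3. Size of that cell**

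Let *m* be the share of followed patients with MMSE at baseline and *t* the share followed by telephone. The protocol gives neither, so both are assumptions. If they are independent, the share with a full MoCA change is (1 − m)(1 − t):

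- m = t = 10%: 0.9 × 0.9 = 0.81
- m = t = 30%: 0.7 × 0.7 = 0.49
- m = t = 50%: 0.5 × 0.5 = 0.25

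Independence is also an assumption. Without it the share lies between max(0, 1 − m − t) and 1 − max(m, t). At m = t = 30% that is 1 − 0.6 = 0.40 to 1 − 0.3 = 0.70.

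**Step 4. Is the Blaylock Score repeated?**

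- *For repetition:* the follow-up item uses the same variable, independence in ADLs and iADLs, that the baseline section ties to the Barthel and Blaylock. The endpoint is defined in Blaylock points. The Statistical analyses section models independence in both domains at baseline and follow-up.
- *Against taking it as settled:* the item stands among questions put to the patient, several of them about perceived change, and apart from the repeated assessments. It includes ADLs although the Barthel Index is already listed. Other instruments to be repeated are named and cited, and this one is not. At baseline the Blaylock belongs to an assessment done by ward medical staff.

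Repetition is therefore implied but not stated.

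**The case against.** The strongest reply on independence is that iADLs are measured at follow-up. The item is in the text, it carries the variable name tied to the Blaylock at baseline, and telephone patients complete the additional questionnaires, which most naturally include it. Figure 1 and the full protocol are not shown and may name the form. This stands in large part. A reader might infer that the iADL component is missing from every follow-up and that the composite reduces to Barthel change. The documents do not support that: iADL information is planned, and what is missing is the name of the instrument. What remains is that a primary endpoint written in points of a named scale should have that scale named where it is collected.

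On cognition, the reply is that it is no endpoint, that no cognitive change score is specified in the analysis section, and that three categories could be assigned from either test. The first two points stand and limit the weight of the finding. A reader might infer that the mismatch touches the primary endpoint; it does not. The third stands only in part: categories may bridge MMSE and MoCA in clinic, but they are coarse, and recall and fluency alone give no total score from which to assign one.

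The percentages can also be challenged, because both shares are assumed. They show how the loss behaves over a range and do not estimate it.

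**Conclusion.** The point holds in two parts of different weight.

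- **Cognition.** This is a stated mismatch. As written, MMSE-baseline patients have no like-for-like change and telephone patients have no total score. About 81% to 25% of followed patients would have a full MoCA change if the MMSE and telephone shares were each 10% to 50% and independent. It affects a stated follow-up aim, but no primary or secondary endpoint.
- **Blaylock Score.** This is an ambiguity in how one of the two components of the longitudinal primary endpoint is collected. No size can be put on it, because sites may already be repeating the scale. The cross-sectional primary endpoint, the ASAS-R, is unaffected.

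The severity is moderate to low. The text does not show that the longitudinal primary endpoint cannot be computed, so treating this as a fault that must be repaired before the study can be relied on would go too far.

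**What to change.** **Cognition**

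- At follow-up, repeat the test the patient had at baseline, which means the MMSE for those who started on it.
- Use the MoCA for all new baselines while enrolment is open.
- For MoCA-baseline patients, analyse change on the recall and fluency items, which clinic and telephone share.
- Analyse MMSE-baseline patients who are followed by telephone, or who have already been retested with the MoCA, separately or by cognitive category where one is available.

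**Independence**

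- Name the Blaylock Score in both the clinic and the telephone follow-up sets, so that the iADL half of the composite is like-for-like. If sites already use it, this is one clarifying phrase. If not, it adds the five iADL areas listed at baseline to an interview already being held.

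**Cost**

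- Testing changes slightly at four hospitals.
- The shared-item analysis uses a coarser cognitive measure than the full MoCA.
- Collection began in April 2023 (Trial status), so patients already followed may have no matching value.

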### Statistical analyses

The multitude of variables included in the present data collection will allow for an encompassing exploratory and confirmatory analysis of the data. The main goal is to (a) identify the parameters that influence self-management, (b) assess how *self-management* influences future daily *functioning/independence*, and (c) estimate the association between *self-management* abilities and *QoL*. Therefore, as a first step, the *self-management* behaviours of older adults at baseline and their gradient until follow-up will be described. Regression with elastic net regularization [62] or (generalized) linear mixed models (LMMs/GLMMs) will be employed for cross-sectional and longitudinal data to understand how the included health-related, psychosocial, and environmental factors influence self-management as the outcome variable (ASAS-R) [49, 50].

Likewise, mixed models, structural equation (SEM) [63–65] and network analyses [63, 64] will be used to explore the association between *self-management* levels at baseline, and *independence* in ADLs and iADLS at baseline and follow-up. These analyses will furthermore be conducted to understand how baseline *self-management* and related variables influence the *QoL*.

Further exploratory analyses may address the influence of baseline self-management abilities on health outcomes at follow-up, the relative influence of *depressive symptoms* and *VoA* on self-management and health outcomes, and the interactive associations among predictors of self-management as assessed via network analysis or structural equation modelling (SEM).

Similarly, irrespective of self-management, the present data collection will provide a rich understanding of the prevalence and impact of geriatric syndromes in older adults and their impact on *self-management* and ADLs/iADLs.

All analyses will be conducted with a significance level of *p* = 0.05; 95% confidence intervals and effect sizes will be reported, wherever appropriate.

## Discussion

Using a comprehensive, observational, and longitudinal approach, the goals of the planned study are (a) to provide a comprehensive overview of self-management abilities, barriers, and opportunities specific to the older patient population, as they are particularly vulnerable; and (b) to evaluate the impact and prevalence of geriatric syndromes as a potential basis for intervention targets.

As stated in the Background section, there is no universally accepted definition of self-management [16, 19]. For the purpose of this data collection, we thus aim to capture the known predictors and facilitators of self-management in the included questionnaires to confirm their impact on self-management. Self-management in this data collection is preliminarily defined as suggested by The Institute of Medicine based on the framework by Lorig and Holman [66], taking into consideration *all* behaviours performed with the goal to improve health [16]. Those behaviours are assessed by the PAM [47, 48] and ASAS-R [49, 50], as both questionnaires enquire after the general ability to perform “activities” or “measures” concerned with health [47–50]. Previous definitions of self-management postulate that several conditions must be in place to facilitate self-management, such as social support, access to healthcare and information, and appropriate environmental standards [16, 34, 67]. In detail, Lorig and Holman [66] identified five central aspects of self-management, namely active participation, problem-solving and decision-making skills, appropriate usage of available resources, and a sustainable patient-provider relationship. Pearce and Parke [67] provided a more detailed framework, including 14 components describing actions both for the patient and the health care provider, such as information exchange, monitoring, support and access, training, and psychosocial strategies. Other similar self-management concepts include person-oriented attributes, such as active participation, responsibility, and coping with setbacks, as well as person-environment factors, including information regarding the illness, treatment options, individualised care, and reciprocal relationships with health care providers [34]. Udlis [16] identified several necessary self-management steps in concept analysis and concluded that “self-management may occur when the individual has the resources and knowledge needed to adhere to a mutually agreed upon plan while actively participating in the management of their chronic illness”, citing self-efficacy, intention, responsibility, knowledge, resources, and cooperation with health care providers as necessary building blocks of self-management behaviour [16]. All these frameworks highlight the need to not only focus on medical aspects, but also incorporate the biological, psychological, and social aspects of self-management [20].

To confirm the influence of these theoretical factors on patient behaviour, the following parameters are included in the data collection: PAM [47, 48] and ASAS-R [49, 50] cover active participation, knowledge, monitoring of symptoms, and self-efficacy. Additionally, self-efficacy is covered in detail in the Generalized Self-Efficacy Scale [51] and the KKG [55, 56]; as further measures of motivation and activation, mental health is addressed with the BAI and GDS [46, 52]. The WHOQOL-Bref not only provides overall information on *QoL* but also details on living conditions and social networks [54]. This encompassing data collection then serves as a guide for deriving a detailed definition of self-management.

A large variety of self-management endpoints and conceptualizations were used in previous studies [14, 34, 68]. In order to comprehensively evaluate the effectiveness of *self-management*, a thorough understanding of various related factors is needed, such as health and *healthcare utilization*, *QoL*, and daily life *independence*. Although initial findings suggest a correlation between *self-management* and unfavorable health outcomes, it is imperative to identify the most practical and viable endpoint to develop effective clinical interventions [6–8]. Therefore, the current data collection will provide an extensive range of information on health-related and psychosocial variables to determine their connection to self-management.

Finally, it should be noted that several studies and interventions have focused on particular diseases [28–30] and may not be customised to meet the unique needs of the older population. One of the challenges of advanced age is the change in health, social networks, and emotional well-being, making older adults particularly vulnerable [69]. At the same time, advanced age also provides unique skills and resources, such as experience, wisdom, free time, or close family bonds, which should be incorporated as intervention resources [69, 70]. The lifelong learning theory postulates that behavioural changes and adaptation are still possible in older age, although they take longer and are more effortful, thus this particular population has specific needs that many health-behaviour interventions do not take into account [69, 70]. Thus, in the face of demographic change and the high level of healthcare utilization in this population [1, 2], the lack of suitable self-management interventions is a grave oversight. To provide this patient population with suitable interventions, in-depth research on self-management and its accompanying constructs is necessary to facilitate best possible care, reduce healthcare utilization, and maintain independence [16, 19, 34, 67].

### Limitations

The study protocol has certain limitations that should be acknowledged. The primary aim of this study is to assess the factors that affect the ability of elderly patients to independently manage their health. This group of patients is highly vulnerable to multiple health issues, chronic illnesses, and declining health. While this approach may restrict the applicability of the results, it is crucial to improve self-management in this population, as they are the most frequent users of healthcare services. This will not only improve their health and independence but also help healthcare systems deal with demographic changes. Additionally, most questionnaires used in this study rely on self-report. However, this is reasonable since self-management is linked to motivation and each individual’s personal perception of what is achievable [16, 34]. All utilised questionnaires are validated. Finally, although this study protocol describes a multicenter study, it cannot be ruled out that the specifics of the German healthcare system may influence the self-management needs and barriers of the included patients.

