## Methods/design

This study is part of a larger project aimed at improving self-management through an intervention trial. The manuscript outlines the procedure for collecting baseline and follow-up data, which will serve as the foundation for the intervention. The first objective of this data collection is to determine the prevalence and impact of geriatric syndromes in order to identify intervention targets that are relevant to the older population. The second objective is to understand the current self-management behaviour and abilities of older adults, including predictors, burdens, and barriers. This will help us understand the link between self-management and health outcomes, and identify the variables that need to be fostered to enable older adults to self-manage geriatric syndromes. The study procedure is described in detail below.

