*Self-management* assessed by the Patient Activation Measure (PAM) [47, 48] and Appraisal of Self-Care Agency Scale-Revised (ASAS-R) [49, 50], with the former primarily assessing *confidence* in self-management abilities, and the latter evaluating self-management *behaviour*.*Self-Efficacy* as assessed by the generalised self-efficacy scale [51].*Anxiety* measured with five items from Becks Anxiety Index (BAI) [52] according to the scale used in the Survey of Health, Aging, and Retirement in Europe (SHARE) [53].Quality of Life (*QoL*) as assessed by the short form of the WHO-Quality of Life Questionnaire (WHOQOL-Bref) [54]. This questionnaire also covers satisfaction with social network, mental and physical health, and living environment.Health Locus of Control (*HLC*) as assessed by the German Fragebogen zur Erhebung von Kontrollüberzeugungen zu Krankheit und Gesundheit (KKG) [55, 56].Views on aging (*VoA*) and subjective age as assessed by the questionnaire used in the German Ageing Survey (Deutscher Alterssurvey, DEAS) [57, 58].

To determine the occurrence and significance of geriatric syndromes, the next step is to utilise a self-created questionnaire using Visual Analogous Scales (VAS). Patients will be requested to select the geriatric syndrome that they are experiencing from a list of options (multiple choice), and to indicate the syndrome that has the greatest impact on their lives (single choice):

Impaired mobility (walking, stairs).Gait problems, falls.Cognitive decline/memory problems.Depressive symptomology.Loneliness.Pain.Incontinence.Sleeping problems.Dysphagia.

Patients are then asked to indicate on a scale of 0 to 100,

how much the respective syndrome affects their daily life,whether they would attribute the syndrome to an illness (0) or old age (100),how worried they are that the respective syndrome will worsen,and how confident they are that the syndrome will improve.

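### The limitations call every questionnaire validated, but syndrome occurrence, part of the first objective, is assigned to a self-created self-report list, and the role of existing instruments in the prevalence estimate is not stated

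*Protocol article*

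**What the plan says.** Under Methods/design, the protocol article sets out its leading aim: "The first objective of this data collection is to determine the prevalence and impact of geriatric syndromes". The stated purpose is to find intervention targets that matter to older people.

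Under Variables and data collection, the tool for this is named: "To determine the occurrence and significance of geriatric syndromes, the next step is to utilise a self-created questionnaire using Visual Analogous Scales (VAS"). Occurrence is recorded by the patient: "Patients will be requested to select the geriatric syndrome that they are experiencing from a list of options (multiple choice"). Patients then name the syndrome with the greatest impact and rate, from 0 to 100, its effect on daily life, its attribution to illness or age, their worry and their confidence in improvement. The list has nine entries. The same scales are repeated at both follow-ups.

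The same section lists baseline assessments by ward staff. Among them are mobility "as measured by the Timed Up and Go (TuG) [44] and Tinetti-Test [45"), cognition by MoCA or MMSE in three grades, the GDS for depressive symptoms, and the UCLA three-item scale for loneliness. Their stated role is that of independent variables related to self-management. The section's opening also names medical records and routine clinical assessments among the sources of information on geriatric syndromes.

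The Limitations section concedes that most questionnaires are self-report, defends this by reference to self-management and motivation, and adds, without exception: "All utilised questionnaires are validated".

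**The concern.** The validation statement cannot be squared with a questionnaire that the authors describe as their own and for which they report no validation. It stands in the section where a reader looks for warnings about measurement, and the tool it overlooks is the one expressly assigned to syndrome occurrence.

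The defence of self-report in that section does not reach this use. A patient's own view is a reasonable measure of self-management and of how much a syndrome bothers them. It is a weaker measure of whether cognitive decline or a gait problem is present. On cognitive grounds, Settings and participants excludes only acute delirium and severe dementia, and it allows consent by a representative. Some patients who are asked to tick their own memory problems will therefore be cognitively impaired.

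At stake is the choice of intervention targets. For five syndromes the study will hold two measures at baseline, and the article does not say which one defines prevalence or how the two relate.

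**Working it through.** The article gives no figure for this point, so the check is a comparison of text and a count.

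**1. Validation statement against the tool.** Limitations says all questionnaires are validated. Variables and data collection says that the syndrome questionnaire is self-created. No validation of it is mentioned anywhere in the article. The two statements conflict.

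**2. List entries against named baseline instruments.**

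| Syndrome on the list | Named baseline instrument |
|---|---|
| Impaired mobility | TuG, Tinetti |
| Gait problems, falls | TuG, Tinetti |
| Cognitive decline | MoCA or MMSE |
| Depressive symptoms | GDS |
| Loneliness | UCLA three-item scale |
| Pain | none |
| Incontinence | none |
| Sleeping problems | none |
| Dysphagia | none |

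Five of nine entries have an instrument. The first two share the same pair of tests, so the five come from four assessment domains. The GDS and the loneliness scale are also answered by the patient; what they add is a published scale. Independence from self-report is gained for mobility, gait and cognition.

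**3. Which source defines prevalence.** Occurrence is expressly assigned to the list. The instruments are given a role as predictors of self-management. The opening of the section names routine clinical assessments as a source on syndromes. Statistical analyses promises prevalence results from the data collection as a whole and names no source. So the role of the instruments in the prevalence estimate is left open.

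**4. Can a bias be calculated?** With true prevalence p, sensitivity Se and specificity Sp, the reported prevalence is p·Se + (1 − p)(1 − Sp). The documents give none of the three. All values below are assumptions, with Sp = 0.90:

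- p = 0.40, Se = 0.50: 0.40 × 0.50 + 0.60 × 0.10 = 0.26, which is 14 points too low.
- p = 0.40, Se = 0.80: 0.40 × 0.80 + 0.60 × 0.10 = 0.38, which is 2 points too low.
- p = 0.20, Se = 0.80: 0.20 × 0.80 + 0.80 × 0.10 = 0.24, which is 4 points too high.
- With Se = 0.80 the bias is zero at p = 0.10 / (0.10 + 0.20) = 0.33.

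For scale, the 95% sampling half-width at p = 0.40 and the planned 265 patients is 1.96 × √(0.40 × 0.60 / 265) = 0.059, about 6 points. Depending on the inputs, the bias is well above this or well inside it, and it can take either sign. The calculation shows only that misclassification could matter.

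**5. When both sources are available.** At clinic follow-up the TuG, Tinetti, MoCA and GDS are repeated, but the loneliness scale is not listed. Patients followed by telephone have the GDS, no TuG or Tinetti, and only recall and fluency from the MoCA. A comparison for all five syndromes is possible at baseline only.

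**The case against.** A reader might infer that the instruments are not used for prevalence, or that occurrence is determined by the list alone. The documents do not support that. The section's opening counts routine clinical assessments among the sources on geriatric syndromes, giving the instruments one role excludes no other, and the derivation for each syndrome is detail that an article may leave to a fuller document.

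A reader might also infer that self-report under-counts syndromes and so mis-ranks the targets. That does not follow either. The sign of the error depends on unknown inputs, and mis-ranking needs error that differs between syndromes, which nothing in the documents quantifies.

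It is also fair to say that perceived burden is a large part of what the authors want. They seek targets relevant to older people and ask about impact, worry and confidence. For that purpose what patients say they experience is a legitimate measure, and replacing it by test cut-offs would be partly a matter of preference. The instruments do not map perfectly: TuG and Tinetti serve two entries, one of which includes falls, and cognition is measured on one of two scales. The article openly calls the tool self-created and concedes reliance on self-report. Neither primary endpoint, the ASAS-R or the independence composite, uses the list.

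All of this limits the point. It does not rescue the validation statement, and it does not remove the case for showing both measures where both exist.

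**Conclusion.** The statement that all questionnaires are validated is wrong as written. This is certain from the text and does not depend on any document not shown. It matters because the tool it overlooks carries the occurrence part of the first objective.

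The second part is narrower. Occurrence is assigned to a self-created self-report list, and the article does not say how the instruments for five of the nine syndromes enter the prevalence estimate. Because patients with cognitive impairment short of severe dementia or acute delirium are eligible, misclassification is plausible, most of all for cognitive decline. Its size and direction are unknown, and no numerical bias should be attached to the plan.

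The change is worth making and the cost is low. The primary endpoints are unaffected.

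**What to change.** In Limitations, restrict the validation statement to the published instruments, and list the syndrome questionnaire as self-created, self-reported and not validated.

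For impaired mobility, gait problems, cognitive decline, depressive symptoms and loneliness, report baseline prevalence twice, as self-reported and by the instruments already in the assessment. Fix the cut-offs before analysis, separately for MoCA and MMSE. Show the two side by side with agreement, for example kappa, overall and by cognitive category. For the cognition entry itself the category is the instrument result, so kappa within a category is undefined; give the proportion of patients in each grade who selected the entry instead. State that the mobility tests do not measure falls directly.

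Label pain, incontinence, sleeping problems and dysphagia as self-reported only. Keep the visual analogue ratings as the measure of perceived impact.

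The cost is a wording change, the pre-specification of cut-offs and a few extra tables. No new data items are needed, since collection is ongoing with these instruments included. The full comparison is confined to baseline.
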